## Abstract

**Background:**

Stable angina pectoris (SAP) currently seriously threatens the health of humans, and mortality is continuously rising. Current treatment strategies mainly include pharmaceutical therapy and revascularization. In China, Buyang Huanwu granules (BYHW) and Naoxintong capsules (NXT) have been used in the treatment of SAP, but it is not clear which agent is better in terms of relieving symptoms and improving quality of life. Therefore, we designed a clinical trial to compare the efficacy and safety of NXT and BYHW in the treatment of SAP.

**Methods:**

This is a randomized, blinded, parallel controlled, multicentre clinical trial protocol. On the basis of standardized Western medicine treatment, a total of 128 SAP patients will be randomly divided into intervention group 1 (NXT group), intervention group 2 (BYHW group), and a control group (placebo group) at a 2:1:1 ratio. A 2-week run-in period is required prior to randomization, and a 1-week baseline period and 4-week treatment period are included in this study. The primary outcome is the efficacy rate of stable angina symptom score improvement; the secondary outcomes include the effect on electrocardiograms, Seattle Angina Questionnaire scores, and nitroglycerine consumption.

**Discussion:**

This study will evaluate the efficacy and safety of NXT and BYHW in the treatment of SAP. The results will provide critical evidence for using Chinese herbal medicines to treat SAP.

**Trial registration:**

Chinese Clinical Trials Registry ChiCTR1800015191. Registered on 13 March 2018. http://www.chictr.org.cn/showproj.aspx?proj=25818. All the registration items can be found within the protocol.

## Administrative information

Note: the numbers in curly brackets in this protocol refer to SPIRIT checklist item numbers. The order of the items has been modified to group similar items (see http://www.equator-network.org/reporting-guidelines/spirit-2727-statement-defining-standard-protocol-items-for-clinical-trials/).

## Introduction

### Background and rationale {6a}

In recent years, cardiovascular disease has been one of the major causes of death globally, seriously threatening human life and health [1, 2]. The mortality rate due to cardiovascular diseases accounts for more than 40% of all-cause deaths in China [3]. Coronary artery disease (CAD), a common cardiovascular disease, is the leading cause of morbidity and mortality worldwide [4, 5]. Angina pectoris is the most common symptom of CAD and a major cause of disability. Stable angina pectoris (SAP), as one of the common types of angina pectoris, is a chronic medical condition with an appreciable incidence of acute coronary events and increased mortality [6]. In 2017, the prevalence rate of SAP was 3.6% in China [7], and the numbers are rapidly increasing due to ageing, dramatic lifestyle changes, and expanding populations with multiple risk factors for angina pectoris, such as hypertension and diabetes mellitus. SAP significantly influences patients’ quality of life and places a heavy burden on society and health care systems [8]. As a consequence, it is now urgent that society mounts a comprehensive attack on SAP, harnessing all available resources to slow, arrest, and possibly even reverse the epidemic of cardiovascular diseases [9].

The aim of SAP management is to stop or minimize symptoms and to improve quality of life and long-term morbidity and mortality. Management options include lifestyle advice, drug treatment, and revascularization using percutaneous or surgical techniques [10]. Pharmacological therapy is safe and beneficial for most patients and remains the cornerstone treatment for SAP. Optimizing pharmacological therapy includes nitrates, beta-blockers, calcium channel blockers, antiplatelet agents, angiotensin-converting enzyme inhibitors/angiotensin receptor blockers, statins, etc. [11]. Despite advances in drug treatment and revascularization strategies over several decades, the prognosis of patients with SAP remains poor, and the rates of mortality and rehospitalization are still high [11]. An increasing number of SAP patients are turning to complementary and alternative medicine to address the symptoms and signs of the disease.

The haemodynamic change caused by early coronary artery disease or atherosclerosis is the basic mechanism of SAP [11], which is similar to the perspective of traditional Chinese medicine (TCM) [12]. TCM has been used in China for more than 2000 years and plays a significant role in the treatment of SAP. Using the theoretical basis of TCM and modern complementary and alternative medicine, Buyang Huanwu granules (BYHW) and Naoxintong capsules (NXT) are widely used in the treatment of SAP, and both have been shown to be effective for patients with SAP [13–16]. Modern clinical studies have shown that BYHW and NXT are both similar prescriptions for protecting vascular endothelial function, delaying the process of atherosclerosis, improving haemorheology indices, reducing blood lipids, and exerting anti-inflammatory and antithrombotic effects and have obvious protective effects on myocardial ischaemia-reperfusion injury [14–17]. Although BYHW and NXT have similar efficacy and application, their constituent herbs are different (Table 1), and there are no prospective data comparing the efficacy of the two in the treatment of SAP. Therefore, we designed a randomized, blinded, parallel controlled, multicentre clinical trial to compare the efficacy and safety of NXT and BYHW in the treatment of SAP.

**Table 1 Tab1:** Characteristics of the investigational product

**Study drug 1: Naoxintong capsule**	
♦ Ingredients: *Astragalus mongholicus* Bunge [Fabaceae; Radix Astragali], *Hirudo nipponia* Whitman [Hirudinidae; Whitmania pigra Whitman], *Boswellia carteri* Birdw., [Burseraceae; Boswellia carterii], *Commiphora myrrha (T.Nees) Engl.,* [Burseraceae; Myrrha], *Salvia miltiorrhiza* Bunge [Lamiaceae; Salviae Miltiorrhizae Radix Et Rhizoma], *Achyranthes bidentata* Blume [Amaranthaceae; Achyranthes], *Neolitsea cassia* (L.) Kosterm. [Lauraceae; Cassia Twig], *Morus alba* L. [Moraceae; Mulberry Twig], *Spatholobus suberectus* Dunn [Fabaceae; Caulis Spatholobi], *Buthus martensii* Karsch [Buthidae; Scorpion];	
♦ Property: capsule; the contents are brown to black brown powder; bitter in taste;	
♦ Specification: 0.4 g/ capsule;	
♦ Bach number: 200593.	
**Placebo 1: Capsule placebo**	
♦ Ingredients: corn starch, silica, caramel (liquid), 2% NXT powder and sunset yellow; ♦ With identical colour, specification, packaging, property of contents and other features with Naoxintong Capsule;	
♦ Bach number: 200501.	
**Study drug 2: Buyang Huanwu granule**	
♦ Ingredients: *Astragalus mongholicus* Bunge [Fabaceae; Radix Astragali], *Angelica sinensis* (Oliv.) Diels [Apiaceae; Angelicae Sinensis Radix], *Paeonia lactiflora* Pall. [Paeoniaceae; Paeoniae Radix Rubra], Lumbricus rubellus (*Oligochaeta*, Lumbricidae), *Ligusticum chuanxiong* Hort. [Apiaceae; Chuan xiong Rhizoma], *Carthamus tinctorius* L. [Asteraceae; Carthami Flos], *Prunus persica* (L.) Batsch [Rosaceae; Semen Persicae].	
♦ Property: granule; the contents are brown to black brown granules; bitter in taste;	
♦ Specification: 5.5 g/ bag;	
♦ Bach number: 200603.	
**Placebo 2: Granule placebo**	
♦ Ingredients: dextrin, 1% Ligusticum chuanxiong, bitterness SA, stevioside, lemon yellow, and chocolate brown; ♦ With identical colour, specification, packaging, property of contents and other features with Buyang Huanwu granule;	
♦ Bach number: 200601.	

### Objectives {7}

The objectives of this study were (i) to evaluate the efficacy of NXT and BYHW in the treatment of SAP and (ii) to test whether NXT is more advantageous than BYHW for treating SAP.

### Trial design {8}

This study is a randomized, blinded, multicentre parallel-group, placebo-controlled clinical trial. The study consists of a 2-week placebo run-in period, a 1-week baseline period, and a 4-week treatment period. The specific study procedures are shown in Fig. 1.

**Fig. 1 Fig1:**
[figure not shown]
Study flowchart

NXT and BYHW are both prescriptions for Qi invigorating, blood circulation activating, stasis removing, and collaterals dredging [18, 19]. NXT was proposed from BYHW and adds blood-activating herbs and collateral-releasing herbs [18]. Over the past two decades, NXT has been used in treating more than 100 million patients, and published more than 1000 academic papers on its clinical or basic researches were reported [15–18]. From clinical experience, in terms of improving symptoms, NXT is better than BYHW, but there is a lack of clinical research evidence. Therefore, we designed this study to compare the efficacy and safety of NXT and BYHW in the treatment of SAP. In addition, based on ethical considerations, we hope that more patients will benefit from this trial. Thus, the eligible patients will be randomly allocated to intervention group 1 (given NXT and a granule placebo), intervention group 2 (given BYHW and a capsule placebo), and control group (given the granule placebo and the capsule placebo) at a ratio of 2:1:1.

## Methods: participants, interventions, and outcomes

### Study setting {9}

This trial will be conducted at six participating sites, including the Second Affiliated Hospital of Zhejiang Chinese Medical University, Hangzhou Xiaoshan District Hospital of Traditional Chinese Medicine, Lishui Hospital of Traditional Chinese Medicine, Fenyang Hospital of Shanxi Province, Affiliated Hospital of Shanxi Chinese Medical University, and Luohe Hospital of Chinese Medicine.

### Ethical review and general statements

This trial has been approved by the Research Ethics Committee of the Second Affiliated Hospital of Zhejiang Chinese Medical University (No. 2017-Y-070-01) and has been registered at the Chinese Clinical Trials Register (ChiCTR1800015191). To guarantee standardized processes and the safety of all participants, our study will be performed in accordance with the principles of Good Clinical Practices (GCP), recommendations of the CONSORT [20] and SPIRIT [21] statements, and the Helsinki Declaration. All participants will be informed about every detail of the trial and will provide written informed consent according to the Helsinki Declaration before participating. To protect the participants’ privacy, the data forms and eCRFs involved in this study will be maintained in secure storage at the coordinating centre.

### Eligibility criteria {10}

Patients will be included after providing written informed consent and enrolled in the study when the inclusion and exclusion criteria are met.

#### Inclusion criteria

Patients will be eligible for this study if they strictly meet the following criteria.
Aged 40 to 75 years, both males and femalesDiagnosis with SAP by the “Guidelines for diagnosis and treatment of chronic stable angina pectoris in 2007” [22] and the “ACC/AHA2002 guideline update for the management of patients with chronic stable angina” [23]Consistent with the diagnostic criteria of grade I~III SAPHistory of SAP within 1 month or myocardial infarction (MI) 3 months priorHaving undergone coronary revascularization or cardiac pacemaker surgery and, after 3 months of treatment, still having SAPVolunteering to participate and sign informed consent

#### Exclusion criteria

Patients who have any of the following criteria may not participate in this test.
History of MI or coronary revascularization or cardiac pacemaker installation within 3 monthsAbnormal electrocardiogram (ECG) and ST segment decline of more than 1 mm in resting 12-lead ECGAcute MI, severe angina pectoris, pulmonary embolism, aortic dissection, cardiomyopathy, aortic valve stenosis and other heart valve diseases, congenital heart disease, left bundle branch block, or electrolyte disturbanceChest pain caused by severe cardiovascular neurosis, climacteric syndrome, cervical spondylosis, bone and joint diseases, digestive system diseases, and respiratory system diseasesSevere liver and kidney dysfunction (including dialysis treatment) and active liver disease (including primary biliary cirrhosis and unexplained persistent liver dysfunction) and/or alanine aminotransferase (ALT), aspartate aminotransferase (AST) > 1.5 times the normal upper limit, creatinine (Cr) > the normal upper limit, and total bilirubin (TBIL) ≥ 2 times the normal upper limitHaving other severe cardio-cerebrovascular, liver, kidney, and haematopoietic system diseases or having recently undergone major surgeryPsychiatric disorders, severe depression, alcohol addiction, or history of substance abusePregnancy or lactation or a positive pregnancy test at the time of admissionAllergic constitution or allergy to the study drugs and their ingredientsParticipation in other clinical trials in the previous 3 monthsPatients who are judged as inappropriate by investigators

#### Who will take informed consent? {26a}

The recruitment of participants in this study will be carried out in the outpatient clinic. When potential participants are in the clinic, the investigator will evaluate their eligibility according to the inclusion and exclusion criteria. Then, trained study staff (physicians or psychologists) will provide verbal information about the trial, answer questions, and obtain written informed consent from potential trial participants. After informed consent obtained, the participants will enter the run-in period.

#### Additional consent provisions for collection and use of participant data and biological specimens {26b}

On the consent form, participants will be informed that their data will be anonymized. This trial does not involve collecting biological specimens for storage.

### Interventions

#### Explanation for the choice of comparators {6b}

Given the complexity of SAP and the urgent need for evidence-based therapy approaches, we chose to add TCM on the basis of standardized treatments and compare the efficacy of NXT and BYHW in relieving stable angina symptoms (including the frequency of angina attacks, duration and degree of pain).

The two intervention groups, i.e. the NXT group and BYHW group, will be compared to the placebo group to evaluate the efficacy of NXT and BYHW in the treatment of SAP. Furthermore, the NXT group will be compared to the BYHW group to evaluate whether NXT is more advantageous than BYHW for treating SAP.

#### Intervention description {11a}

Eligible participants will experience a 2-week run-in period, a 1-week baseline period, and a 4-week treatment period. The interventions during the treatment period are shown in Table 2, and details are as follows:

**Table 2 Tab2:** Intervention implementation plan

Intervention groups	Naoxintong capsule	Capsule placebo	Buyang Huanwu granule	Granule placebo
**Intervention group 1**	✓			✓
**Intervention group 2**		✓	✓	
**Control group**		✓		✓

Intervention group 1 will receive NXT (0.4 g/capsule, op, 4 capsules/tid) and a granule placebo (5.5 g/bag, op, 1 bag/tid).

Intervention group 2 will receive BYHW (5.5 g/bag, op, 1 bag/tid) and a capsule placebo (0.4 g/capsule, op, 4 capsules/tid).

The control group will receive the capsule placebo (0.4 g/capsule, op, 4 capsules/tid) and the granule placebo (5.5 g/bag, op, 1 bag/tid).

Placebo drugs will be given for 2 weeks during the run-in period, followed by the appropriate medication for a 4-week intervention period.

Standardized treatment: During the run-in and intervention periods, according to the guidelines for SAP treatment, participants will receive standardized treatment consisting of aspirin, statins, ACEIs, and/or ARBs. Substitution with TCM having a similar composition and/or efficacy to NXT or BYHW is not permitted. If instances of an angina attack occur, participants should take one nitroglycerine tablet under the tongue at a time and can repeat one tablet every 5 min until the pain is relieved. If the pain persists after the total amount reaches three tablets within 15 min, medical attention will be immediately requested.

The following concomitant therapies will be permitted, provided the regimen has been stable for the specified period of time prior to the first dose of study drug and the dose remains the same with no increase or decrease during the study treatment period:
Beta blockers, antiplatelet therapy, statins, angiotensin-converting enzyme inhibitors, and angiotensin receptor blockers will be allowed provided the dose has been stable for at least 4 weeks prior to the run-in period. If instances of an angina attack occur, nitroglycerine tablets can be used sublingually.During the intervention period, when combined medication is required for other diseases, the investigator should record the name of the medication, the reason for the medication, and the time of medication in detail.If infection, hyperglycaemia, hypertension, etc., are present in the intervention period, symptomatic drugs will be allowed provided the therapy does not affect the efficacy and safety of the test drug. All drugs used must be recorded for analysis and reporting in the summary.

The following medications are prohibited throughout the duration of the study treatment period. If banned drugs are used, those subjects will be withdrawn from the study.
Long-acting nitratesChinese medicinal preparations that are used for the treatment of coronary heart disease or may have the effects of promoting Qi, promoting blood circulation and removing blood stasisAnticoagulant drugsOther drugs that may affect the evaluation of test drugs

In this study, NXT, BYHW, the capsule placebo, and the granule placebo are provided by Shaanxi Buchang Pharmaceutical Co. Ltd. The capsule and granule placebos are similar to the study drug in smell, colour, specification, packaging, property of contents, and other features.

#### Criteria for discontinuing or modifying allocated interventions {11b}

Participants are allowed to withdraw at any time without having to give a reason. The withdrawal criteria are as follows: (1) participants request withdrawal from the study; (2) there is exacerbation or deterioration that is clearly related to the treatment; (3) an allergic reaction that is clearly associated with the study drug occurs; (4) participants show comorbidities, complications, adverse events (AEs), or serious adverse events (SAEs) during the trial; (5) there is use of forbidden drugs or receipt of prohibited treatment; (6) participants show poor adherence, or the amount of drug used does not meet the regulations (< 80%); and (7) blinding is uncovered or emergency unblinding is required.

If a subject withdraws from the trial, no additional data will be collected, but the existing data will be used for statistical analysis. The time of treatment or trial discontinuation and the reason for withdrawal will be documented on the CRF. Drop-out patients will not be replaced.

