#### Strategies to improve adherence to interventions {11c}

Low adherence can have a substantial effect on statistical power and biased estimates of an intervention’s effect. To improve adherence to intervention protocols, during the treatment phase, we will distribute medicines once a week to evaluate the participant’s drug consumption and monitor adherence in a timely manner. Face-to-face adherence-reminder sessions will take place during the medicine dispensing process. After treatment, the drug package will be returned to the researchers. Compliance will be self-reported by participants and will be assessed by investigators at each visit. Compliance is calculated using the following formula: compliance = (actual amount of internal use/total amount of internal use) × 100%. Poor compliance is predefined as compliance < 80%. After 28 days of treatment, participants with poor compliance will be removed from the per protocol set (PPS).

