#### Relevant concomitant care permitted or prohibited during the trial {11d}

Concerning standardized treatment, during the run-in period and treatment period, aspirin, statin lipid-lowering drugs, angiotensin converting enzyme inhibitors (ACEIs), or angiotensin receptor blockers (ARBs) should be used. TCM formulations with a similar composition and efficacy to those of study drugs will not be allowed to be used. Researchers should record the concomitant medication accurately and maintain dose stability during the trial. The participants should be clinically stable for the last 1 month or receiving standardized treatment for ≥1 month with no modification of dosage or intravenous administration.

Concerning emergency care, in the event of an acute angina pectoris attack during treatment, participants should be treated with nitroglycerine first (one tablet at a time, by sublingual administration, which can be repeated every 5 min until the pain is relieved). If the pain persists after the total amount reaches 3 tablets in 15 min, medical attention should be sought immediately. The treatment status should be recorded. If the participant’s condition deteriorates during treatment and it is not advisable to continue the trial, the researcher should consider terminating the trial and switching to surgery or another type of clinical treatment, and the patients will be classified in the analysis as “treatment ineffective”.

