### Outcomes {12}

#### Primary outcome

The primary outcome is the efficacy rate of stable angina symptom score classification [24]. The stable angina symptom score includes the attack frequency, duration, activity level of effort-induced angina pectoris, and pain degree. The indicators of the baseline period (0 weeks) and treatment period (28 days) will be compared.

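### Withdrawal criterion 4 covers any comorbidity, complication or adverse event without qualification, and so conflicts with the rule that treatable events are managed and recorded on study

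*Protocol article*

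**What the plan says.** Section {11b} of the protocol article gives seven withdrawal criteria. The fourth reads "4) participants show comorbidities, complications, adverse events (AEs), or serious adverse events (SAEs) during the trial" and carries no qualifier. The second does carry one, "2) there is exacerbation or deterioration that is clearly related to the treatment", and the third likewise requires a clear link to the study drug. Once a patient is withdrawn, "If a subject withdraws from the trial, no additional data will be collected", and existing data are analysed.

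Section {11a} deals with intercurrent illness: "If infection, hyperglycaemia, hypertension, etc., are present in the intervention period, symptomatic drugs will be allowed", as long as the therapy does not interfere with assessing the test drug. All drugs used are recorded. Withdrawal is ordered there only for banned drugs.

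On the primary outcome, the article says "The indicators of the baseline period (0 weeks) and treatment period (28 days) will be compared". Table 4 schedules the symptom score at those two times only. Section {20c} fills missing values by last observation carried forward (LOCF). It defines the full analysis set (FAS) as every randomised patient with at least one dose.

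**The concern.** An infection or a rise in blood pressure during the four treatment weeks is treated and recorded on study under {11a}, yet is a listed ground for withdrawal under {11b}. Both rules are printed and they disagree, so this is more than a detail left out of a condensed article. Six sites could handle the same event differently.

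What is at stake is the primary analysis. A patient withdrawn for a treated infection would be scored as if the angina had not improved, although the event says nothing about angina response. Section {11d} already classes patients stopped for deterioration as treatment failures, which is a reasonable choice for that group. Read literally, criterion 4 gives the same result to events unrelated to efficacy.

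**Working it through.** **1. The two rules side by side.**

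- Event: infection, hyperglycaemia or hypertension arising in the intervention period.
- Under {11a}: symptomatic treatment allowed, drugs recorded, no withdrawal.
- Under {11b}, criterion 4: a comorbidity, complication or AE, hence a withdrawal criterion.
- Qualifier: present in criteria 2 and 3, absent from 4.

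**2. What follows if criterion 4 is applied before the day-28 score.** No further data are collected ({11b}). The only symptom score on file is the baseline one (Primary outcome, Table 4); weekly dispensing visits exist ({11c}), but no score is scheduled at them. LOCF therefore puts the baseline score at day 28, so change is zero. The article does not print the responder cut-off, but zero change cannot be an improvement. The patient remains in the FAS ({20c}) as a non-responder.

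The per-protocol set (PPS) is not fully protected. Section {20c} requires eligibility, at least 80% compliance and no prohibited drugs, but not completion. If compliance is measured against 28 days of drug, 0.80 × 28 = 22.4 days, so a late withdrawal could stay in the PPS with the baseline score carried forward.

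**3. The plan's own sample size.** Inputs from Sample size {14}: rates of 85%, 70% and 50%, alpha 0.05, df 2. With equal weights w and mean rate p̄, W = √[Σ w(p − p̄)² / (p̄(1 − p̄))] = 0.30821. Then 102 × 0.308210² = 9.689, which gives power 0.8024 (beta 0.1976), as stated. 102 / 0.80 = 127.5, rounded up to 128. The total is reproduced.

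**4. Effect of one patient.** Each true responder withdrawn early under criterion 4 lowers the FAS rate by 1/64 = 1.56 points (NXT) or 1/32 = 3.13 points (BYHW or placebo).

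**5. Illustration.** The documents give no withdrawal rate for AEs, so the rates a below are assumptions. FAS rate = planned rate × (1 − a), where a is the share of the arm withdrawn under criterion 4 before the day-28 score. This assumes that those patients would have responded at their arm's planned rate. Power is for the three-group chi-square with all 128 analysed at 2:1:1. With those weights W is 0.3216, so the first row differs from the plan's 0.80 at N = 102.

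| a, %: NXT / BYHW / placebo | FAS rates, % | NXT − BYHW | NXT − placebo | BYHW − placebo | Power |
|---|---|---|---|---|---|
| 0 / 0 / 0 | 85 / 70 / 50 | 15 | 35 | 20 | 0.913 |
| 2 / 2 / 2 | 83.3 / 68.6 / 49.0 | 14.7 | 34.3 | 19.6 | 0.892 |
| 5 / 5 / 5 | 80.75 / 66.5 / 47.5 | 14.25 | 33.25 | 19.0 | 0.856 |
| 5 / 5 / 2 | 80.75 / 66.5 / 49.0 | 14.25 | 31.75 | 17.5 | 0.825 |
| 5 / 2 / 2 | 80.75 / 68.6 / 49.0 | 12.15 | 31.75 | 19.6 | 0.824 |
| 2 / 5 / 2 | 83.3 / 66.5 / 49.0 | 16.8 | 34.3 | 17.5 | 0.894 |

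Across these rows the shifts run from 3.25 points down (35 to 31.75) to 1.8 points up (15 to 16.8). Setting one arm at 5% and another at 0% is more extreme: NXT minus placebo becomes 0.85 × 0.95 − 0.50 = 30.75 points (4.25 down), and NXT minus BYHW becomes 0.85 − 0.70 × 0.95 = 18.5 points (3.5 up). In patients, 5% is 3.2 of 64 or 1.6 of 32; 2% is 1.28 or 0.64.

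**The case against.** The best defence is that the list states possible grounds, not automatic triggers. Criterion 6, poor adherence, is clearly not automatic, because {11c} says "After 28 days of treatment, participants with poor compliance will be removed from the per protocol set (PPS". Section {22} has AEs followed with duration, treatment and outcome, which is hard to square with every AE ending participation. Read literally, criterion 4 also makes criteria 2 and 3 largely redundant. Section {11b} records the time of treatment or trial discontinuation, so stopping the drug need not mean leaving the trial. And an article may shorten a fuller criterion.

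Much of this stands as evidence of intent, and a reader should not conclude that every AE will in fact lead to withdrawal. It does not settle the wording. Section {11d} leaves stopping to judgement, "it is not advisable to continue the trial, the researcher should consider terminating the trial", but that concerns deterioration and mainly parallels criterion 2. Section {22} does not say that a patient with an AE continues, and it mentions reactions that disappear once the drug is stopped. No sentence tells a site that {11a} overrides criterion 4.

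Three stronger readings are tempting, and the documents do not support them:

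- **That criterion 4 catches the many patients who enter with hypertension or diabetes.** The background section does name "multiple risk factors for angina pectoris, such as hypertension and diabetes mellitus", but that is epidemiology. Criterion 4 concerns what patients show during the trial, and nothing says that a pre-existing condition triggers it.
- **That carrying the baseline forward is a product of criterion 4.** It follows from LOCF with a single post-baseline score and affects every early dropout. Criterion 4 adds only the extra withdrawals it causes.
- **That the PPS analysis is immune.** The 80% rule does not ensure it, as shown in the working.

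**Conclusion.** The conflict between {11a} and criterion 4 of {11b} is real and should be corrected. If the criterion is applied literally before day 28, a patient with a treatable, unrelated event becomes a FAS non-responder by the plan's own rules.

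The size is unknown and probably small. Section {22} expects side effects in a small number of patients, although criterion 4 also covers unrelated comorbidities and complications. At the assumed 2% or 5% the effect on between-arm differences is modest, and three-group power stays above 0.80 in every row of the table. The bias can run in either direction when arms differ.

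A reader might infer a serious loss of power, since 10% such withdrawals in every arm would give 0.791 and 20% would give 0.651. The documents do not support using those rates: 20% is the allowance for dropout from all causes, and no rate for criterion 4 is given. This point shows no stated sample-size or power figure to be wrong. Confidence is medium, because the list may be meant as discretionary.

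**What to change.** Reword criterion 4 so that it applies only to comorbidities, complications, AEs or SAEs that, in the investigator's judgement, make continued study treatment unsafe or inadvisable. Add that events treatable under {11a} are treated and recorded, with the patient kept in the trial and scored at day 28. Notify the six sites.

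The cost is a short amendment to the withdrawal criteria and a site note. Visits, sample size and randomisation do not change. The drawback is timing: the article reports recruitment in progress, so patients enrolled before and after the amendment may be handled differently. Record the amendment date and report criterion 4 withdrawals by arm before and after it. A note saying that {11a} governs treatable events would be lighter, but would leave the conflicting sentence in the protocol.
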